# An exploratory single arm study to evaluate the role of an Ayurvedic treatment protocol as a prerequisite for *in vitro* fertilization in women with diminished ovarian reserve incorporating multi-omics approaches: study protocol

**DOI:** 10.3389/fmed.2025.1666888

**Published:** 2025-11-25

**Keywords:** diminished ovarian reserve, multi-omics, anti mullerian hormone (AMH), antral follicle count (AFC), Integrative medicine, traditional medicine, *in vitro* fertilization, ayurveda

## Abstract

**Introduction:**

Ovarian reserve depicts the quality and quantity of oocytes remaining in the ovaries and gives an idea about ovarian function at a given time. Because of aging, ovarian reserve diminish physiologically. However, many women face a non-physiologic reduction of ovarian reserve, irrespective of age. To date, standard-of-care treatment options are not available to treat diminished ovarian reserve (DOR). Studies shows that DOR patients mostly undergo *in vitro* fertilization (IVF) with donor cycles. Hence, identifying effective treatment modalities for DOR is an area of great clinical relevance. This trial will investigate the role of an Ayurvedic treatment protocol in DOR patients prior to IVF. Reports suggest that the factors influencing oocyte maturation can be determined through multi-omics analysis of the follicular fluid. However, the impact of Ayurvedic interventions in improving therapeutic outcomes has yet to be explored in detail. Hence this study also aims to explore whether therapeutic targets can be identified through multi-omics analysis of the follicular fluid collected from the participants after Ayurvedic treatment.

**Materials and methods:**

An open label single arm trial will be conducted to explore the role of an Ayurveda treatment protocol as a prerequisite for IVF in women with DOR. Forty women diagnosed with DOR satisfying eligibility criteria will be recruited to the study. Out of them, thirty participants will be undergoing Ayurveda treatment prior to their next IVF, and ten participants will be assigned to control group for follicular fluid analysis. Within subject change in serum anti-mullerian hormone and antral follicle count will be the primary outcomes evaluated. The multiomics analysis of follicular fluid will be done in 20 participants recruited to the study (treatment group 10 and control group 10).

**Discussion:**

This multidisciplinary exploratory clinical trial will be the first study to explore the role of an Ayurvedic treatment protocol in managing DOR. The multi-omics approaches will be helpful in identifying potential biomarkers associated with treatment response. The information gained through the study might be useful in planning a safe and feasible pre-conception care for DOR patients undergoing IVF.

**Clinical trial registration:**

ctri.nic.in, identifier CTRI/2023/11/059872.

## Introduction

Infertility is a disorder that impacts an individual’s psychological and social aspects (1). The treatment of infertility is mainly focused on its cause. With the advancement in medical sciences, assisted reproductive technique (ART) can now overcome major issues causing infertility (2). But the successful outcome of all these treatment modalities is completely based on one’s ovarian reserve. Ovarian reserve depicts the quality and quantity of oocytes remaining in the ovaries (3). It thus gives an idea about ovarian function or reproductive age at a given time. Because of aging, ovarian reserve diminish physiologically. But many women face a non-physiologic reduction of ovarian reserve, irrespective of age. The non-physiological reduction may result from multiple factors like autoimmune diseases, environmental pollution, psychological factors, genetic factors, endometriosis, pelvic inflammatory disease and chemotherapy (3). It has been reported that DOR is one of the leading reasons for seeking ART, with approximately 26% of patients undergoing ART due to this condition (4). DOR may be associated with irregular menstruation, hypomenorrhea, amenorrhea, short follicular phase, and poor ovarian response (5). Clinical assessments of DOR are done through ultrasonography by counting the number of ovarian antral follicles (AFC), and serum anti-mullerian hormone (AMH) test (6). DOR patients are being managed through conventional medicine by different stimulation protocols, Hormone replacement therapy (HRT), and Dehydroepiandrosterone (DHEA) as pre-treatment to IVF. It was observed that even after ovarian hyperstimulation with high-dose gonadotrophin, DOR patients have a smaller number of oocytes, a low fertilization rate, and a higher cycle cancellation rate (7). Most patients are ultimately left with the only option of IVF with a donor egg (8). But proper evidence is lacking to support their role in DOR (9). Also, the mode of action of these medicines is still unknown (10). Hence, identifying effective treatment modalities for DOR becomes an area of great clinical relevance.

Although there is no direct explanation of DOR in Ayurvedic texts, the clinical manifestations of certain gynaecological conditions show remarkable similarity. One such disorder is ārtavakṣaya, a menstrual abnormality arising from the depletion (kṣaya) of ārtava upadhātu (the supportive component of reproductive system), which closely parallels DOR in both its etiology and presentation. The clinical presentations of ārtavakṣaya is also evident in several endocrine disorders such as polycystic ovarian syndrome (PCOS), hyperprolactinemia, and thyroid dysfunction, as well as in physiological states like the premenopausal period, DOR, and premature ovarian failure (POF). Regardless of the underlying cause, these conditions share a common pathophysiological mechanism which involves dysregulation of the hypothalamo- pituitary -ovarian axis resulting in oligo or anovulation and manifesting clinically as oligomenorrhea or hypomenorrhea.

Ayurveda similarly attributes ārtavakṣaya to either qualitative or quantitative reduction of ārtava which possess agneya guna (fire element) characterized by yadocitakāla adarśana (irregular menstruation/oligomenorrhea), alpata (scanty menstruation/hypomenorrhea), and yonivedana (pain in vagina). The therapeutic approach in Ayurveda primarily aims to restore the function of ārtava. Management is two-fold, śodhana karma (cleansing therapy) and śamana karma (medicines for restoring normalcy or pacifying action). Śodhana may be achieved through vamana karma (therapeutic emesis) or virecana karma (therapeutic purgation), depending on the patient’s condition, followed by śamana therapy using medicines possessing agneya guṇa (to enhance fire element) (11). Ayurveda also emphasizes comprehensive preconception care which also includes basti karma (therapeutic enema) including uttarbasti (administration of therapeutic oil or ghee via vagina) after śodhana karma to optimize the quality of strībījam (ovum) and prepare the woman for healthy conception (12). In our clinical experience, several women diagnosed with DOR who underwent Ayurvedic interventions based on ārtavakṣaya cikitsā and preconception care protocols at our centre demonstrated notable improvement in serum AMH levels, subsequently becoming eligible for ART using their own oocytes (13). A few even achieved spontaneous conception during treatment. The group of formulations selected in this protocol was chosen for their established indications in restoring ārtava and facilitating preconception care. The specific medicines were selected based on each patient’s clinical condition and presentation. These encouraging outcomes underscore the potential role of Ayurveda in the management of DOR and highlight the need for generating the preliminary evidence for a safe and feasible Ayurveda treatment protocol. In the future, it will help to plan further clinical studies which may benefit DOR patients to have ART procedures with their eggs, thus opening a wide scope for research in integrated medicine.

In addition, the possibility of identifying detailed pharmacological mechanisms that might improve the therapeutic outcomes in DOR patients can be explored by incorporating multi-omics analysis. The role of proteomics, metabolomics, and transcriptomics in the analysis of human follicular fluid has been reported previously by several groups (14–16). Reports suggest that the factors influencing oocyte maturation can be determined by analysing the follicular fluid proteome (14, 17). Proteomics analysis of follicular fluid indicated the pharmacological mechanisms of Chinese patented drugs for improving DOR (18). Similarly, various groups have also identified serum metabolite markers for predicting poor ovarian reserve (19, 20) Also, transcriptomics analysis indicated that several genes are modulated in DOR patients (21). All these indicated that the pharmacological mechanisms induced by Ayurvedic treatment could be studied using multi-omics analysis to identify therapeutic targets. All these give an overall idea of how genes and proteins influence the quality of embryo and oocyte maturation, thereby improving therapeutic outcomes. However, the impact of Ayurvedic interventions in improving therapeutic outcomes has yet to be explored in detail. The pharmacological mechanisms induced by Ayurvedic treatment could be studied using multi-omics analysis to identify therapeutic targets, such as genes/proteins involved in oocyte development including steroidogenesis, oxidative stress, cumulus-oocyte signalling. Thus, the aim of this study is to explore the feasibility and within-subject changes in AMH/AFC and generate mechanistic hypotheses. The information gained through the study might be useful in planning future research which may help to incorporate a feasible Ayurvedic pre-conceptional care for DOR patients undergoing ART procedures. Similarly, the possibility of identifying therapeutic targets through multi-omics analysis can be studied.

## Materials and methods

This is a prospective, exploratory, single-arm, open-label, single-centred study, coordinated by Amrita Fertility Centre, Amrita School of Ayurveda, and Amrita School of Biotechnology, India with two assessment points (baseline and post-intervention). Participants are women diagnosed with DOR undergoing fertility treatments. Women under the age of 40 satisfying all the eligibility criteria and willing to provide informed consent will be recruited from Amrita Fertility Centre, Kochi. Recruited participants will be admitted at Amrita School of Ayurveda, Kollam to undergo a standardized Ayurvedic treatment protocol for a maximum period of 21 days. Following the inpatient treatment, participants will be advised to continue prescribed internal medications for an additional 1 month. After undergoing Ayurveda treatment, participants will be sent back to Amrita Fertility Centre for post-assessment and further fertility treatments, during which follicular fluid will be collected for multi-omics analysis. Figure 1 depicts the trial’s participant flow. The Standard Protocol Items: Recommendations for Intervention Trials (SPIRIT) declaration is followed while reporting the protocol (22). The institutional ethical committee approved the study and is prospectively registered under ctri.nic.in with the number CTRI/2023/11/059872 on November 15, 2023.

**Figure 1 fig1:**
[figure not shown]
Trial participant’s flowchart.

### Sample size

The sample size calculation was done using G*Power (version 3.1.9.7) (23) based on a previous study data. The initial sample size calculated to detect an effect size of 0.58 for a two-sided significance level of 0.05 and 80% power was 26. To account for feasibility considerations and an anticipated 20% dropout, the final sample size was set at 30 participants. Since the present study is planned as an exploratory study, this sample size is not meant to give confirmatory inference, rather this study is planned to provide preliminary data regarding the role of an Ayurvedic treatment protocol in women with reduced ovarian reserve.

Follicular fluid will be collected from 10 participants who undergo Ayurveda treatment and 10 control participants who is receiving a contemporaneous IVF stimulation protocol for performing multi-omics analysis (matched by age and baseline AMH/AFC). No formal sample size calculation was performed for the multi-omics analysis, as it is hypothesis-generating and intended for exploratory purposes. Because the 10 controls included are for exploratory multi-omics analysis only, no clinical inference will be drawn between treatment and control groups.

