## Statistical methods

The AMH and AFC changes within the 30 participants who underwent Ayurveda treatment will be assessed using paired *t*-tests (if the data is normally distributed) or Wilcoxon signed-rank test (if the data is non-normal), as determined by Shapiro–Wilk test. Statistical significance is considered as *p* < 0.05 for all two-sided tests. Results will be reported as mean ± SD or median (IQR), with effect sizes (Cohen’s d) for pre-post changes. As a sensitivity analysis, ANCOVA will be utilized for adjusting post-treatment data for baseline AMH/AFC and variables such as age, BMI, and ovarian response.

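### Thirty participants do not absorb the anticipated 20% dropout from a required 26: 30 covers about 13%, and at 20% dropout 24 pairs give about 78% power

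*Protocol article*

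**What the plan says.** The Sample size section of the protocol article names G*Power as the software and gives one calculation: "The initial sample size calculated to detect an effect size of 0.58 for a two-sided significance level of 0.05 and 80% power was 26". The next sentence moves from that figure to the recruitment target: "To account for feasibility considerations and an anticipated 20% dropout, the final sample size was set at 30 participants". The abstract, Trial settings and Statistical methods all keep 30 as the number treated.

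Statistical methods says that the changes in AMH and AFC "will be assessed using paired" t-tests, with a switch to the "Wilcoxon signed-rank test (if the data is non-normal" as judged by a Shapiro–Wilk test). The Sample size section also says that the study is exploratory and that its size is not intended for confirmatory inference.

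**The concern.** Three numbers stand side by side: 26 needed, 20% expected to be lost, 30 recruited. The text presents the third as allowing for the second, and the arithmetic does not bear that out. If dropout is as high as the plan itself expects, fewer pairs remain than its own calculation requires.

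This is the only power calculation in the article. At stake is whether it describes the study that will be run: a reader would take it that the 26 pairs are protected against the anticipated loss, and they are not.

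**Working it through.** **Inputs**, all from the Sample size section unless noted:
- effect size d = 0.58
- two-sided alpha = 0.05
- target power 80%
- calculated size 26
- anticipated dropout 20%
- recruitment target 30
- test: paired t-test (Statistical methods)

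**Step 1. Reproduce the 26.** For n pairs, the paired t-test has n − 1 degrees of freedom and noncentrality d√n. Two-sided power is P(|T| > t(0.975, n − 1)), where T follows the noncentral t distribution.

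| Pairs n | 0.58 × √n | t(0.975, n − 1) | Power |
|---|---|---|---|
| 24 | 2.841 | 2.069 | 77.7% |
| 25 | 2.900 | 2.064 | 79.5% |
| 26 | 2.957 | 2.060 | 81.1% |
| 30 | 3.177 | 2.045 | 86.7% |
| 33 | 3.332 | 2.037 | 89.8% |

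The smallest n that reaches 80% is 26, so the stated figure reproduces. It is the minimum number of evaluable pairs and has no dropout margin in it.

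**Step 2. Inflate for 20% dropout.**
- Correct form: 26 / (1 − 0.20) = 32.5, so 33. Check: 33 × 0.80 = 26.4.
- Common mistaken form: 26 × 1.20 = 31.2, so 32.

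Neither gives 30.

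**Step 3. Work back from 30.**
- Pairs left after 20% dropout: 30 × 0.80 = 24, two fewer than 26.
- Dropout that 30 can absorb while keeping 26: (30 − 26)/30 = 4/30 = 13.3%.

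**Step 4. Consequence at 24 pairs.**
- Power for d = 0.58 is 77.7%. That is 80.0 − 77.7 = 2.3 points below target and 81.1 − 77.7 = 3.4 points below the power at 26.
- Solving the same power formula for d at n = 24 and 80% power gives d = 0.597, about 0.60 instead of 0.58.

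**Step 5. Could 30 come from another starting figure?** The normal approximation gives ((1.960 + 0.842)/0.58)² = 23.3, so 24, and 24/0.80 = 30. That would fit, but the article states 26, so it does not reconcile the two sentences.

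**The case against.** **Feasibility.** The sentence gives two reasons for 30, and feasibility comes first. It can be read as a compromise in which practical limits stopped recruitment short of 33. That is a fair explanation of why 30 was chosen, and it counts against calling this a plain miscalculation. It does not make 30 sufficient for 20% dropout, and nowhere does the article say that a lower power, or 24 completers, was accepted.

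**Exploratory status.** The article says that the size is not for confirmatory inference, and its Limitations section calls the findings preliminary and hypothesis-generating. This stands as a reason to rate the point as minor. It does not correct the figure.

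**A stronger reading: the promised 80% power is not delivered.** A reader might infer this, but the article attaches 80% to the initial figure of 26 only. It states no power for 30 recruited or for 24 completers. The shortfall also arises only if dropout goes beyond 13.3%; up to that level 30 meets or exceeds 80%. What the text supports is narrower: 30 does not fully offset the dropout it is said to account for.

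**A second stronger reading: the Wilcoxon fallback lowers power further.** A reader might multiply n by 0.955, the test's large-sample efficiency for normally distributed differences. But the plan uses Wilcoxon only when the data are judged non-normal, so that factor belongs to the case in which the test is not meant to be used. A simulation with 24 pairs and a standardised mean change of 0.58 (20,000 runs per shape) gives Wilcoxon power of about 75% for normal differences, 80% for logistic, 84% for t with 5 degrees of freedom and 85% for Laplace. These shapes are assumptions, all symmetric, and others could differ. The documents support no single figure, and planning on the parametric test is ordinary practice.

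**Conclusion.** Wrong as written, and minor. Thirty participants cover about 13% dropout from a requirement of 26, not the stated 20%. Full cover would take 33. If the anticipated 20% is lost, 24 pairs remain and paired t-test power for 0.58 is about 78%, with 80% reached only at an effect size of about 0.60.

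The dropout arithmetic rests only on the three printed numbers. The power figures also assume a paired t-test, normally distributed differences, and 0.58 as the standardised within-subject change; the exact reproduction of 26 supports that last reading. A shortfall of 2.3 points in a study declared non-confirmatory changes neither the design nor what may be concluded from it.

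**What to change.** Replace the sentence that sets the final size with wording such as:

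> For feasibility, 30 participants will be recruited; with 20% dropout, 24 evaluable pairs give about 78% power by paired t-test for an effect size of 0.58; at least 80% power is kept if dropout is at most about 13% (26 pairs).

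This removes the claim that 30 accounts for 20% dropout. Do not add a power figure for the Wilcoxon test, because it depends on the unknown non-normal shape of the differences.

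The cost is one sentence and a slightly less favourable power statement. Recruitment, analysis and conduct are unchanged.

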### Trial settings

The participants will be screened for eligibility at Amrita fertility centre, Kochi. After baseline assessment of AMH and AFC on day 2/3 of the menstrual cycle, 30 participants who are satisfying the eligibility criteria will be recruited for the study and will be admitted for Ayurveda treatment at Amrita School of Ayurveda, Kollam for a maximum of 21 days. On discharge, participants will be dispensed with internal medicines for 1 month. Post assessment will be done at Amrita Fertility Centre on day 2/3 of their next menstrual cycle which comes after completing 1 month of internal medications. Follicular fluid will be collected on the oocyte retrieval day of their next IVF cycle for multi-omics analysis (Treatment group—10 and Control group—10). The participant timeline is detailed in Table 1. The sample collected will be then transferred to Amrita School of Biotechnology for multi omics analysis.

**Table 1 tab1:** Participant timeline.

Time point	Study period				
	Visit 0—screening visit	Visit 1—baseline visit—Day 2/3 of the first menstrual cycle	Visit 2—Day 3/4 of the first menstrual cycle	Visit 3—Day 2/3 of the third menstrual cycle	Visit 4—oocyte pick up day of next IVF cycle
Enrollment					
Eligibility screen	X	X			
Informed consent		X			
Demographic information		X			
Intervention					
Initiation of Shodhana/cleansing (for a period of 18–21 days) followed by Shamana (internal medicines) for a period of 1 month at Amrita school of Ayurveda			X		
Assessments					
Serum AMH at Amrita fertility centre				X	
Ultrasound scan for AFC at Amrita fertility centre				X	
Collection of follicular fluid at Amrita fertility centre					X
Adverse events monitoring(throughout the intervention period)			X		

AFC, antral follicle count; AMH, anti-mullerian hormone.

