#### Inclusion criteria

Women aged 25–40 yearsWho are willing to provide written informed consent to participate in the clinical trialA confirmed diagnosis of DOR fulfilling at least two of the Bologna criteria, namely:
an abnormal ovarian reserve test, defined as an AFC of <5–7 follicles and/or AMH level of <0.5–1.1 ng/mL; anda history of poor ovarian response, defined as retrieval of ≤3 oocytes in a previous IVF cycle.

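### The Visit 1 AMH/AFC reading both qualifies a woman and serves as her 'before' value, so regression to the mean biases both primary outcomes upward, by an amount the protocol does not fix

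*Protocol article*

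**What the plan says.** Under Trial settings in the protocol article, the baseline measurement comes first and recruitment of eligible women follows: "After baseline assessment of AMH and AFC on day 2/3 of the menstrual cycle, 30 participants who are satisfying the eligibility criteria will be recruited". Table 1 marks the eligibility screen at Visit 0 and again at "Visit 1—baseline visit—Day 2/3 of the first menstrual cycle".

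The inclusion criteria require a diagnosis "fulfilling at least two of the Bologna criteria". Only two are then listed, so both are needed. One is "an abnormal ovarian reserve test, defined as an AFC of <5–7 follicles and/or AMH level of <0.5–1.1 ng/mL"; the other is three or fewer oocytes retrieved in a previous IVF cycle. The AMH/AFC criterion is therefore compulsory and cuts on the low side only.

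The Outcomes section places the before-treatment value for both AMH and AFC on day 2/3 of the first cycle, at recruitment. The analysis in Statistical methods is within-group: "The AMH and AFC changes within the 30 participants who underwent Ayurveda treatment will be assessed using paired" t-tests, or the Wilcoxon signed-rank test, at p < 0.05 "for all two-sided tests", with Cohen's d reported. A baseline-adjusted ANCOVA is the sensitivity analysis. Sample size rules out clinical inference from the ten controls. The Limitations cover the single arm and the surrogate markers but not regression to the mean.

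**The concern.** A woman's AMH or AFC varies between readings. If she enters because one reading is low, that reading will on average lie below her own usual level, and the next will on average be higher with no treatment effect. Here the qualifying reading is reused as the 'before' value, so this rise goes straight into the estimated change.

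The bias runs in the hypothesised direction on both primary outcomes, and nothing in the plan removes it. The controls are not compared on AMH or AFC. ANCOVA within one arm has no comparator against which to separate regression from treatment. A single laboratory, scanner and operator reduce measurement error but not cycle-to-cycle variation. At stake are the size of the reported change and the error rate of the two primary tests.

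**Working it through.** **1. The plan's own figure.** For a paired t-test with effect size 0.58 and two-sided alpha 0.05, the exact noncentral-t power is 0.811 at n = 26 (noncentrality 0.58 × √26 = 2.96) and 0.795 at n = 25. The stated 26 is reproduced, and 0.58 serves below as the yardstick.

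**2. Inputs.**
- From the document: low-side cut on AFC and/or AMH; compulsory poor-response history; one reading before and one after; n = 30; two-sided 0.05.
- Not in the document, so assumed: test-retest correlation r = 0.95, 0.90, 0.80, 0.70; the proportion p of the source population below each marker's cut; correlation 0.7 between true AMH and true AFC; correlation 0.6 of each with oocyte yield; poor response as the lowest 25% of yield; normality. The printed cuts are ranges, so the truncation point is itself not fixed.

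**3. Selection on one marker, no treatment effect.** With c the p-quantile of the standard normal:
- λ = φ(c)/p
- expected rise = (1 − r)λ, in population SDs
- truncated variance v = 1 − cλ − λ²
- SD of change = √[(1 − r)²v + 1 − r²]
- d = rise / SD of change

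For p = 0.26: c = −0.643, λ = 1.248, v = 0.246. At r = 0.80 the rise is 0.20 × 1.248 = 0.250, the SD is √(0.04 × 0.246 + 0.36) = 0.608, and d = 0.41. The upper-tail rejection probability at n = 30 follows from the noncentral t.

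**4. The rule in the protocol.** Simulation: each reading is √r × true value + √(1 − r) × fresh error. A woman enters if either first reading is below its cut. The last two rows also require low oocyte yield. Results are per marker.

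Null d, with the chance of a significant rise at n = 30 in brackets (nominal 2.5%):

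| Selection rule | r = 0.95 | 0.90 | 0.80 | 0.70 |
|---|---|---|---|---|
| One marker, lowest 26% | 0.20 (18%) | 0.28 (32%) | 0.41 (58%) | 0.51 (78%) |
| One marker, lowest 50% | 0.13 (10%) | 0.18 (16%) | 0.26 (28%) | 0.33 (41%) |
| One marker, lowest 90% | 0.03 (4%) | 0.04 (4%) | 0.06 (5%) | 0.08 (6%) |
| 'And/or', 26% | 0.09 (7%) | 0.12 (9%) | 0.17 (14%) | 0.20 (19%) |
| 'And/or', 50% | 0.05 (4%) | 0.07 (6%) | 0.10 (7%) | 0.11 (9%) |
| 'And/or' + poor response, 26% | 0.05 (5%) | 0.07 (6%) | 0.10 (8%) | 0.13 (10%) |
| 'And/or' + poor response, 50% | 0.02 (3%) | 0.03 (3%) | 0.04 (4%) | 0.05 (4%) |

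The drift is upward in every row. Against the design effect, the 'and/or' rule gives 0.05/0.58 = 9% to 0.20/0.58 = 34%. With the poor-response history it is 0.02/0.58 = 3% to 0.13/0.58 = 22%.

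**5. After the fix.** If one reading qualifies the woman and a separate later reading is her baseline, the simulated null change is 0.00 SD and the chance of a significant rise is 2.4% to 2.6%. This assumes that chance deviations at the two readings are independent.

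**The case against.** The strongest case against the point concerns its size. Single-marker truncation is not the protocol's rule. Under 'and/or', a woman admitted on AFC need not be low on AMH, and the reverse. A history of poor response is separate evidence that her true reserve is low. Both weaken the drift, and this stands. The 26% in the Introduction is the share of ART patients treated because of DOR, not the share of women at the baseline visit who fall below the cut. Participants are already diagnosed, so that share may be far higher and the drift smaller. This stands too.

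It is also fair that the identity of the two readings is partly inferred. A Visit 0 exists and the diagnosis may rest on an earlier value. Table 1 as available marks AMH and AFC only at Visit 3, so it does not settle the matter. But the eligibility screen is repeated at Visit 1, and any woman whose reading has risen above the cut would be removed there. Some selection on the baseline therefore remains.

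Finally, the article calls itself exploratory and its findings preliminary. That limits what may be concluded from the change; it does not remove bias from it, and testing at 0.05 is still planned.

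A reader might infer that the observed d will be used to size later trials. The document does not say so: it expects future controlled studies to add broader reproductive and clinical endpoints.

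**Conclusion.** The point holds on structure and direction: the AMH/AFC cut is applied, or re-applied, at the visit whose reading is the 'before' value, and nothing in the uncontrolled paired analysis removes the expected upward drift. The size is conditional. For cuts at 26% to 50% and r from 0.95 to 0.70, the null d is about 0.05 to 0.20 under 'and/or', and about 0.02 to 0.13 with the poor-response history. The chance of a significant rise is about 3% to 19% against 2.5%. A less selective cut gives less.

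A tempting stronger reading is that regression to the mean alone will produce an apparent improvement, with d of 0.2 to 0.5 and up to 0.51/0.58 = 88% of the design effect. The documents do not support it. Those values need entry on one marker in the lowest 26%, which is not the rule written. What is supported is an expected upward bias of unknown and possibly small size, not a guaranteed significant result. This is a should-fix point: a cheap improvement rather than a fatal flaw.

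**What to change.** - State that the AMH/AFC criterion is judged on the earlier reading behind the confirmed diagnosis (Visit 0 or the clinic record), and that the cut-off is not re-applied at Visit 1.
- Use the Visit 1 day 2/3 reading as baseline for every enrolled woman, whichever side of the cut-off it falls.
- Name regression to the mean in the Limitations. For women already enrolled with Visit 1 as the qualifying reading, report a sensitivity range such as the one above.
- Do not present the Visit 0 to Visit 1 shift as an untreated comparator for the treatment-period change. Under this scheme the first carries the regression effect and the second does not, so they are unlike quantities.

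The cost is protocol wording, plus one extra screening measurement where no usable earlier value exists. Some baseline values will lie above the cut-off, and the observed change will probably be smaller. Values on file may come from another assay or operator, but this matters only for eligibility, because both readings in the paired test would still be trial measurements.
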